## Abstract

**Background:**

Oral health is an important part of general physical health and is essential for self-esteem, self-confidence and overall quality of life. There is a well-established link between mental illness and poor oral health. Oral health problems are not generally well recognized by mental health professionals and many patients experience barriers to treatment.

**Methods/Design:**

This is the protocol for a pragmatic cluster randomised trial that has been designed to fit within standard care. Dental awareness training for care co-ordinators plus a dental checklist for service users in addition to standard care will be compared with standard care alone for people with mental illness. The checklist consists of questions about service users’ current oral health routine and condition. Ten Early Intervention in Psychosis (EIP) teams in Nottinghamshire, Derbyshire and Lincolnshire will be cluster randomised (five to intervention and five to standard care) in blocks accounting for location and size of caseload. The oral health of the service users will be monitored for one year after randomisation.

**Trial registration:**

Current Controlled Trials ISRCTN63382258.

## Background

Oral health is an important part of physical health and is essential for self-esteem, self-confidence and overall quality of life [1,2]. Oral diseases are the most common chronic disease and have a great impact on individuals [3]. Oral health is not just about having healthy teeth it is a ‘standard of health of the oral and related tissues which enables an individual to eat, speak and socialise without active disease, discomfort or embarrassment and which contributes to general well-being’ [1]. It has often been the case that when a person has a serious mental illness and are unwell, their oral health may not be seen as a priority, so it is neglected and deteriorates [2]. Oral health problems are often not detected by mental health professionals [4] and, to compound the matter, many dentists shy away from treating people with psychosis [5,6].

Research conducted in the last decade that has examined the oral health of people with serious mental illness has generally concluded that oral health for people with serious mental illness is poor compared with the general population [7-11]. People with serious mental illness are likely to experience more oral health problems and require more dental treatment than people from the general population [2]. Side effects of medication prescribed to people with serious mental illness can cause a lack of saliva, which in itself can lead to caries [12-15].

### Guidelines

The British Society for Disability and Oral Health guidelines published in 2000 made a number of recommendations for oral health care for people with mental health problems, including providing oral health advice, support, promotion and education addressing the oral health needs of clients [2]. We are not aware of other guidelines regarding dental care for people who have been diagnosed with serious mental illness, practical advice is missing.

### Surveys

Recent surveys that have described the current oral health of people with serious mental illness in various settings, have concluded that the oral health of people with serious mental illness is poor, and many have indicated that it is significantly worse than the general population [16].

### Systematic reviews

A recent systematic review and meta-analysis of advanced dental disease in people with severe mental illness found that people with mental illness were 3.4 times more likely to have lost teeth than the general population and had higher rates of decayed, missing or filled teeth [17]. A meta-analysis of 57 studies looking at the prevalence of suboptimal oral health of people with mental illness and describing approaches to promote oral health [18], found a suboptimal oral health prevalence of 61% as well as highlighting the need for oral health training for mental health professionals. A recent Cochrane review [19] found no relevant randomised trials comparing an oral health advice intervention with standard care for people with serious mental illness that met the inclusion criteria. Another Cochrane review assessed the effectiveness of physical health monitoring as a means of reducing morbidity, mortality and improving quality of life in people with serious mental illness but also found no trials meeting the inclusion criteria [20].

### Trials

There are very few randomised controlled trials of monitoring or advice regarding physical health care for people with serious mental illness. One small trial randomised sixty people to interventions of motivational interviewing plus oral health education or oral health education alone and found that the oral health of individuals who received the motivational interviewing improved significantly more compared to oral health education alone [14]. Another trial randomly assigned 100 participants to receive professional hygienic training or to a no treatment control group and also compared the effectiveness of the intervention for those treated with classical neuroleptics and atypical neuroleptics [21]. Results showed that the effectiveness of oral hygiene training for people receiving classical neuroleptics was lower than for those receiving atypical neuroleptics.

### Objectives

To examine whether dental awareness training plus a dental checklist leads to a clinically significant difference in oral health behaviour of people with serious mental illness.

### Design

#### Setting

The trial will be conducted as part of standard care provided by the Early Intervention in Psychosis (EIP) teams in Nottinghamshire, Derbyshire and Lincolnshire (UK). These three shires are located in the East Midlands of England and each have a mixture of urban and rural areas with a diverse population. The EIP teams provide intensive treatment and support to people with a first experience of symptoms such as hearing voices or those who develop unusual beliefs which may indicate the onset of psychosis. Care co-ordinators are the main contact person for service users throughout their involvement with the service; it is the care co-ordinators who will be delivering the intervention in this trial to their service users.

The three shires dental trial was designed with considerable collaboration with EIP clinicians and service users to make it acceptable to be delivered with minimal disruption alongside standard care. The dental checklist (see Additional file 1) was adapted from the British Society for Disability and Oral Health (BSDH) guidelines [2] in design workshops with researchers, clinicians, service users and carers.

#### Sample size

No previous trials exist [19]. It is, therefore, difficult to determine the number of people that need to be recruited to generate clinically significant data regarding the effect of an oral health advice intervention on the oral health of people with a serious mental illness. As we designed the study in consultation with clinicians and service users, we tried to gain an impression of the size of difference that would cause a change in practice. We did not formally record these estimates, but consensus suggested a range of between 10% to 20%. We estimate the sample size for the mid-way point (Table 1).

**Table 1 T1:** Sample size needed to detect an absolute difference of 15% in the proportion of visits to a dentist (α = 5%, power = 80%)

**Standard care, %**	**Dental intervention, %**	**Non-cluster N (total)**	**Multiplied by design effect**	**Adjusted for 20% dropout**
5	20	176	334	418
10	25	226	430	538
15	30	268	510	638
20	35	302	574	718
25	40	330	628	785
30	45	352	670	837
35	50	366	696	870

Complicating this further is that this is a cluster trial so the EIP teams will be randomised as a whole team rather than at the individual patient level. Intraclass correlation coefficient (ICC) in cluster trials are difficult to estimate if no previous studies exist and to not take clustering into account would lead to ignoring the potential for a unit-of-analysis error [22-24]. Simply estimating that we will be able to randomise the people for whom the 10 teams provide care into two groups is not an accurate reflection of the power of the study. This has to be multiplied by a design effect to adjust for clustering. There are two levels of clustering within this trial, the EIP teams are the clusters that will be randomly allocated to receive the interventions but there are also clusters within the teams; the individual care co-ordinators. Non-cluster N was calculated using the Stata version 11 software (StataCorp, College Station, TX, USA) with alpha = 0.05, power = 0.80. The design effect (DE) was calculated considering patients clustered within each staff/team and each staff sees 10 patients (DE = 1+ (10–1)*0.1 = 1.9), with an intracluster coefficient of 0.1 as a best guess.

Assuming that 5% of the service users who receive standard care visit a dentist, to then detect a 15% increase in the proportion of those who visit a dentist in the dental intervention arm with 80% power at 0.05 significance level, we need 176 service users for a single-centre trial, after adjusting for the cluster effect by multiplying this by the design effect, we need to recruit 334 service users. After further adjusting for 20% of service users lost to follow up, the final number of service users we need to recruit is 418. Other situations with various proportions of visits to a dentist in standard care are also presented in Table 1.

All these assumptions we have made in this power calculation may be correct or all may be incorrect. It is, at this point, quite impossible to say. As can be seen from the background, no studies have been undertaken in this area. There is no data to even guess what any effect may or may not be. This is a pioneering trial that will set a standard and will allow researchers in the future to have some benchmark off which to work.

#### Ethical considerations

EIP team managers will be asked to consent to the trial being conducted within their teams. Informed consent will be sought from care co-ordinators in accordance with Research Ethics Committee (REC) and Good Clinical Practice (GCP) guidance. Service users will be asked by the care co-ordinator if they agree to the care co-ordinator completing the dental checklist at the time of their regular appointment. Service users will not give formal consent for this trial, agreeing to answer the questions on the dental checklists is their consent. This is standard for routine care and public health measures. This is due to the intervention being aimed at the care co-ordinators who receive the dental awareness training, and it is the effect of this training and the checklist that is being measured and not the responses of each service user. The effect of this combined intervention will influence the service users’ dental awareness, even if they do not complete the checklist. It will be made clear to the service users that they do not have to answer the questions if they wish and this will have no detrimental effect on their standard care. If the need arises, relevant information only will be disclosed to the care co-ordinator or another relevant individual in authority.

The trial has received a favourable opinion from the East Midlands Nottingham Research Ethics Committee (REC reference 11/EM/0205) and from the Nottinghamshire, Derbyshire and Lincolnshire National Health Service (NHS) Research and Development (R&D) departments. The trial team have research passports, GCP training, Criminal Records Bureau checks and letters of access for each NHS Trust.

All data will be made anonymous and stored securely. Changes to the protocol will not be implemented until the amendments or revised documents have received favourable opinion from the REC and R&D departments. A protocol amendment intended to eliminate an apparent immediate hazard to participants may be implemented immediately and the REC will be notified as soon as possible to request approval. Minor protocol amendments for logistical or administrative reasons may be implemented immediately and the REC will be informed.

## Methods

### Randomisation

This is a pragmatic, open, cluster randomised controlled trial. We are limited by the number and size of the teams as well as by the compliance of the care co-ordinators. The Nottingham Clinical Trials Unit (CTU) will create a randomisation program that will be used by the researcher to randomise the EIP teams. The researcher will list the teams in such a way as to anonymise them, we will then block randomise; the block being the number of teams within each county. This will ensure that each county gets some degree of exposure to the intervention. EIP teams will be grouped into pairs according to location and size of team, which will then be randomised with one team being allocated the active intervention and the other the control. Randomisation will be stratified to ensure that both of the interventions are roughly equal in terms of team location, number of care co-ordinators within the team and size of caseloads. The CTU will keep full records of the procedure, but there will be no requirement for having procedures for breaking code.

### Participants

Care co-ordinators will be recruited by the EIP team managers and the trial team, and service users will be recruited by the care co-ordinators. Care co-ordinators will be informed of all aspects concerning participation in the trial.

#### Inclusion criteria

Any EIP team in Nottinghamshire, Derbyshire and Lincolnshire and any service users under the care of a care-coordinator in one of these teams, who is aged 18 years or above will be included. Any concomitant treatments are allowed.

#### Exclusion criteria

Any EIP team that does not wish to take part and any individual care co-ordinator who feels that they do not wish to take part will be excluded. The data from service users under the age of 18 at randomisation will not be collected. People who are unable to provide informed consent will be excluded.

### Removal of participants from therapy or assessments

Teams or care co-ordinators within each team can withdraw at any time. They will have given consent but could decide to withdraw that consent. All data up to the point of withdrawal will be used. Withdrawal from the study would result in resumption of standard care. Service users will be withdrawn if a team or care co-ordinator removes their consent.

Participants may be withdrawn from the trial either at their own request or at the discretion of the Investigator. Service users will be made aware that this will not affect their future care. All participants will be made aware (via the information sheet and consent forms) that should they withdraw the data collected to date cannot be erased and may still be used in the final analysis.

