### Procedure

Before teams are randomised, all managers will be given information sheets and asked to sign a consent form providing permission for their team to be involved in the trial. We will collect demographic information about the EIP teams to create a list of eligible service users and a cross-coding sheet by which each service user can be allocated an anonymous trial ID. Demographic information will include team location, number of care co-ordinators within the team, size of caseloads and distance to dental services from the team base. The trial team will not have access to identifiable NHS data.

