#### Dental intervention

After randomisation, EIP teams allocated to receive the dental intervention will be approached by the trial team to arrange a convenient time to conduct the one-off dental awareness training at the start of the 12-month intervention period. Information sheets will be given out to care co-ordinators and consent forms will be signed. This will fit within the usual multidisciplinary team meetings, but is likely to take around 30 minutes, including time for questions and shared experiences. There will be a manual in order to keep it consistent for all teams (see Additional file 2). The training will briefly cover the aims and background of the trial, how to complete the checklist, service user ID number allocation, how to return the completed checklists to the trial team and discussion about what to do in certain situations regarding adverse events. The care co-ordinators will be encouraged to use the checklist for all their service users at their earliest convenience. The checklist is printed on carbonless copy paper, one copy of the dental checklist will be kept in the service users’ notes and one will be returned in pre-paid envelopes to the trial team. Care co-ordinators will also be encouraged to offer their service users an oral hygiene information sheet which contains oral hygiene tips and information on how to find an NHS dentist (see Additional file 3).

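### Co-ordinators who know their team's allocation can decline or withdraw and take whole caseloads out of the comparison, and the consent-based exclusion contradicts the no-formal-consent design

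*Protocol article*

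**What the plan says.** All references are to the protocol article.

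- **Masking.** The Randomisation section states: "This is a pragmatic, open, cluster randomised controlled trial".
- **Before randomisation.** Under Procedure, managers consent for their teams, and the trial team gathers information to "create a list of eligible service users and a cross-coding sheet by which each service user can be allocated an anonymous trial ID". A cohort can therefore be named before allocation.
- **Co-ordinator consent.** In intervention teams this comes at the contact that arranges and gives the training, after randomisation (Dental intervention): "Information sheets will be given out to care co-ordinators and consent forms will be signed". Under Control group, co-ordinators in control teams are also asked to sign, with no time given, and are asked to use the checklist a year later than the intervention group.
- **Declining.** Under Exclusion criteria, "any individual care co-ordinator who feels that they do not wish to take part will be excluded".
- **Withdrawing.** Under Removal of participants from therapy or assessments, "Service users will be withdrawn if a team or care co-ordinator removes their consent". Data collected before withdrawal are kept.
- **Service-user consent.** Exclusion criteria: "People who are unable to provide informed consent will be excluded". Ethical considerations: "Service users will not give formal consent for this trial"; agreeing to answer the checklist stands in for consent.
- **Losses.** Procedures for missing data plans multiple imputation, or a selection or mixture model, for users who leave early. Secondary outcomes lists leaving the service, with reasons that include refusing consent.

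**The concern.** Randomising teams makes the caseloads comparable only if the people compared are those present at allocation. Here a member of staff who already knows the arm can, by declining or withdrawing, remove every user on a caseload. In the intervention arm, consent commits the co-ordinator to training and checklist work at once. In the control arm the same work is a year away. The conditions under which staff say no therefore differ by arm, and so may the caseloads that are lost.

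The Ethical considerations section makes such removal harder to justify. It says that the effect of the training and checklist is what is measured, and that users can be influenced without completing the checklist. On that reasoning, users of a reluctant co-ordinator belong in the allocated comparison.

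At stake is whether a difference in dentist visits reflects the intervention or the choice of caseloads that stayed.

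**Working it through.** **1. The plan's own figure.** For 5% v 20%, two-sided alpha 0.05, power 0.80, 1:1, with continuity correction: 88 per arm, 176 in total. Times the design effect 1 + (10 − 1) × 0.1 = 1.9 gives 334.4, stated as 334. Then 334 / (1 − 0.20) = 417.5, stated as 418. The figures reproduce, so the planned number is not in dispute. The 20% inflation restores precision only; it does nothing about which users are lost.

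**2. What happens to a listed user.**

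| Event | Rule | 12-month primary outcome | Covered by missing-data plan? |
|---|---|---|---|
| Co-ordinator declines at the outset | Co-ordinator excluded | No route stated | Not clearly; user never entered |
| Team or co-ordinator withdraws during the year | Users withdrawn, earlier data kept | None, because the follow-up checklist is at 12 months | Yes, as an early leaver |
| User judged unable to consent | Excluded; assessor not named | No route stated | Not clearly |

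**3. Unit of loss.** The Sample size section assumes 10 patients per member of staff. Trial status gives 1,074 users in 10 teams (some may be under 18), so about 1,074 / 10 = 107 co-ordinators, and on average also about 107 users per team. If the arms are equal (537 each), one co-ordinator is 10 / 537 = 1.9% of an arm, a tenth of an arm's users is about 54, and one of five equal teams is 20%.

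**4. Illustration of bias with no true effect.** These inputs are assumed. Let p be the true visit rate in both arms, f the fraction lost from the intervention arm only, and k the ratio of the lost users' visit rate to p. The retained rate is (p − f·k·p) / (1 − f), so the spurious difference is p·f·(1 − k) / (1 − f).

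Example: p = 20%, f = 20%, k = 0.5 gives 0.20 × 0.20 × 0.5 / 0.80 = 2.5 points; k = 0 gives 5.0.

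Spurious difference in points, k = 0.5 to k = 0; p is taken from the control rates in Table 1:

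| p | f = 10% | f = 20% | f = 30% |
|---|---|---|---|
| 5% | 0.3–0.6 | 0.6–1.25 | 1.1–2.1 |
| 20% | 1.1–2.2 | 2.5–5.0 | 4.3–8.6 |
| 35% | 1.9–3.9 | 4.4–8.75 | 7.5–15.0 |

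At f = 20% and the design's effective sizes (176, 302 and 366), a nominal 5% two-sided test (normal approximation) would reject in 5.4–6.5%, 8.3–18.0% and 13.9–40.2% of trials for p = 5%, 20% and 35%.

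**5. Sign.** If the lost users visit more often than average, the sign turns: k = 1.5 with p = f = 20% gives 0.20 × 0.20 × (−0.5) / 0.80 = −2.5 points. The same loss from the control arm also reverses it, and equal f and k in both arms cancel. The article gives neither f nor k for either arm.

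**The case against.** The removal rules govern participation and assessment; they do not define an analysis set. No sentence says that withdrawn users leave the denominator, and the analysis detail sits in an additional file that is not shown. The missing-data plan reaches users withdrawn during the year, and reasons for leaving are to be recorded. This stands: the absence of an all-randomised statement is not the fault, and a reader who infers that the analysed groups are certainly not the randomised ones goes too far. What remains is that the stated rules cut off the outcome, and the missing-data plan does not clearly reach caseloads that never entered.

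Four further readings are tempting but not supported:

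- **That the bias favours the intervention.** Control co-ordinators must also consent, so a motivation filter may act in both arms, and its timing there is unstated.
- **That the size is 1.5 to 4.5 points.** If caseloads of declining co-ordinators stay at 5% and the rest reach 20%, the all-randomised rate (1 − f) × 20 + f × 5 is 18.5%, 17% or 15.5% for f = 10%, 20% or 30%, against 20% among those retained. That gap is dilution of an assumed effect. With no effect it is zero, so it does not measure selection bias.
- **That the co-ordinator judges capacity to consent.** No assessor is named. It is a fair inference, since co-ordinators recruit users and the trial team sees no identifiable data. But the exclusion may be meant for the signed consent that the Follow-up section requires for the OIDP interview and dentist records.
- **That people joining a caseload later enter the trial.** The list is drawn up before randomisation and age is fixed at randomisation. The instruction to use the checklist for all of a co-ordinator's users does not settle the matter.

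**Conclusion.** The concern holds as a fault in the stated exclusion and withdrawal rules. In the intervention arm, consent is sought with allocation known; declining and withdrawing each remove a whole caseload; and neither the retention of earlier data nor the missing-data plan fully repairs this. The comparison could be biased, in a direction and by an amount that the article does not allow one to determine. The ranges in the working are scenarios: they rest on assumed loss fractions, loss in one arm only, and assumed lower visit rates among those lost. They show only that losses of a plausible scale could be material against a 15-point target, mainly where the visit rate is 20% or more.

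Separately, the exclusion of people unable to give informed consent contradicts the statement that service users give no formal consent. As written, it cannot be applied consistently. This is a point of clarity, not a demonstrated selection mechanism.

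**What to change.** 1. Define the primary analysis set as all service users aged 18 or over at randomisation on the list made before randomisation, analysed in their team's allocated arm.
2. State that a co-ordinator's refusal or withdrawal ends delivery of the intervention but does not remove users from the denominator.
3. Seek the 12-month outcome for these users by the same route in both arms, as far as ethics approval and the users' own agreement allow. Otherwise treat it as missing under the existing plan, extended to caseloads that never entered, with a sensitivity analysis for data missing not at random.
4. Report refusals, exclusions and withdrawals by arm and reason, building on the leaving-service outcome already planned.
5. At new sites, whose recruitment Trial status describes as under way, obtain co-ordinator consent before the team is randomised.
6. Reconcile the consent exclusion with Ethical considerations: state to which data it applies and who assesses it.

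**Cost.** More missing outcomes, an effect diluted by users who received nothing, and a protocol amendment. Under Ethical considerations, a change that is more than logistical or administrative needs a favourable opinion from the REC and R&D departments. The result is not guaranteed to be unbiased: outcomes in declining caseloads may be missing not at random, so it still depends on the missing-data models. For the 10 teams already randomised, item 5 comes too late, but the other items can still be applied.
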